13. REFERENCES

**1. SUMMARY**

**Title**: Computer supported CEA surveillance after curative treatment of colorectal cancer

**Aim of the study**: The aim of the current study is to develop an evidence-based guideline with standard diagnostic tools (CEA and CT scan) that results in a (cost-) effective recommendation which is applicable for all hospitals in the routine follow-up after curative treatment of colorectal cancer.

**Study design**: In the intervention group follow-up, care consists of bi-monthly CEA measurements starting three months after surgery, a yearly outpatient clinical visit and CT imaging after one and two years. Patients will be closely monitored in an outpatient setting by a frequent testing of CEA, supported by a computer-based system (CEA watch). The patients will be asked to assess their CEA value every 8 weeks. The computer-based system allows us to closely monitor the blood values and to communicate the results to the patient as soon as possible (by e-mail and/or p-mail). In case of two consecutive significant rises in CEA values, extra imaging diagnostics will be performed. In the control group the intervention is follow-up care as usual according to the Dutch national guideline. The starting point of the new regimen will be randomised among the participating clinics.

**Endpoints**: Primary outcome: increase of 15 percent of radical resected metastases in patients as expressed as the percentage of total recurrences. Secondary outcomes: overall survival time cancer specific survival time, time to recurrent disease, quality of life, and costs related to diagnostics.

**Statistics**: Increase in percentage of resected metastases from 10-25% needs 115 patients with metastases in both groups. With an expected recurrence rate of 25%, 460 patients per group are needed. After correction factor about 800 patients per group are needed.

In the economic evaluation costs of both follow-up strategies will be assessed and compared. In addition cost-utility analysis will be conducted based on Quality Adjusted Life Years (QUALY’s).

**Study duration**: The study will be conducted in three years. After a start up period of six months all eligible patients will be identified and registered. Three months later every three months a new pair of hospitals will be randomized to start the new schedule of follow-up and all registered patients will start with the intensive schedule. The last three months will be used for analysis of the data.

**2. INTRODUCTION AND RATIONALE**

*2.1 Introduction / background*

The incidence of metachronous metastases after curative colon and rectum resections is approximately 30-50%, with an increasing incidence dependent on the initial stage. Predominant sites of first recurrence in the population with recurrent disease are the liver (± 40%), lung (± 30%) and local recurrence (± 25%) (Kobayashi). These types of recurrent disease can be eligible for curative resection, which is now feasible in an estimated 10-30%. The increase in survival after metastasectomy for resectable recurrent disease is high, with a 5 year overall survival after metastasectomy of approximately 30% for all three types of recurrent disease (Goldberg, Bentrem, Pfannschmidt). It is predominantly dependent on achievement of a R0 resection and the number of metastases, the last probably corresponding to tumor behaviour.

*2.2. Follow-up*

After curative treatment of colorectal cancer, patient surveillance is recommended to detect curable recurrent disease or new primary tumors in an early phase. There was a statistically significant increase in feasibility of intended curative resection of recurrent disease in 5 prospective randomised studies and in the 5 year overall survival in 4 of the 5 studies. Based on the literature, both the Dutch guideline (CBO 2008), the Canadian guideline and the US guideline (ASCO 2005) propose a high intensity program of regular office visits, imaging studies (CBO: liver ultrasound, Canada: liver imaging, ASCO: Computed Tomography (CT) chest-abdomen) and CarcinoEmbryonicAntigen (CEA) tests. Imaging is advised since not all recurrences are detected with an early CEA raise. The value of physical examination in detecting recurrent disease is low (Borie, Sugarbaker).

*2.3. Carcinoembryonic antigen (CEA)*

Carcinoembryonic antigen (CEA) is a serum tumor marker used in follow-up of colorectal cancer. It is a protein expressed at the surface of endodermal cells during embryological development, where it has a role in cell-to-cell adhesion. In adults, it is expressed in malignancies and benign inflammatory disease of endodermally derived organs, such as the small and large bowel, pancreas, lung and thyroid. Smoking and other malignancies such as breast and ovarian cancer can increase serum CEA as well. Gold and Freedman discovered it as one of the first serological tumor markers in 1965. Staab developed the basis for it’s clinical application around 1980, after which it was introduced in daily clinical practice for colorectal cancer. The advised frequency of CEA testing in guidelines is ambiguous. The Dutch guideline advices CEA measurements every 3 to 6 months for the first 3 years, and every 6 months in year 4 and 5. The US guideline for CEA advices every 3 months for at least 3 years. Furthermore, no advice is given on the interpretation of CEA results. The key to an effective use of CEA is frequent assessment and an interpretation of test results based on the absolute value as well as on the trend in CEA increases (if present). In this way both sensitivity and specificity of CEA testing may be increased. (Steele, Boey, Staab, [name] (b)). Several authors mention the lack of compliance to frequent CEA measuring, especially in the elderly patient (Cooper). However, in our single-centre trial with intensified CEA measurements, compliance of patients was high. ([name], manuscript in preparation) and major part of the problem might be the doctor’s low compliance to the guidelines. As a result, in daily practice a significantly lower frequency of CEA was generally performed; causing a much less effective result of CEA testing ([name](a), Graham, Steele, Minton, [name] (c), Spratlin). With the availability of a computer support system this problem is mostly solved.

*2.4.* *CEA watch*

The innovative element of the study is the introduction of CEA watch. This intranet based program based on open source software: MySQL database, PHP scripting and java. It automatically presents new CEA values of enlisted patient to the interpreting doctor. Normal results of CEA can immediately be sent by e-mail to the patient. A suggestion for a date for a new CEA check is made based on available information. In the case of a rise in CEA the patient will be called and appropriate steps will be made. All results will be sent to the patients by postal mail as well, with a laboratory form for the next CEA check. For this next CEA check the patient can report to the hospital laboratory at a date or time by his own choosing. If a patient seems to forget a CEA check, CEA-watch will issue a reminder. CEA-watch has several advantages for the patient and for the clinic. Outpatient clinic visits are reduced. The patient will come to the outpatient clinic only once a year if the results are normal. This will reduce concerns to the outcome of the disease by the patient and his family, as every outpatient clinic visit is a renewed confrontation with the disease. Furthermore, it will reduce the workload for the outpatient clinic. Compliance to the schedule of frequent testing is achieved by constant monitoring of every individual patient. Patient satisfaction is expected to increase due to the early availability of the result and the reduction of waiting time in the hospital since the patient only has to come to the laboratory at a moment chosen by him. The relevant clinical outcome is the increase in the number of radical resected metastases (lung, liver and peritoneal cavity) with a subsequent increase in cancer-specific survival.

*2.5. Imaging*

CT scanning may be superior to ultrasound in terms of sensitivity, specificity and inter- and intraobserver reliability, but it is more expensive than ultrasound and related to radiation-based health hazards. As the optimal frequency for imaging is not known, it may be expected that the use of ultrasound and CT will increase as will the logistical and financial consequences of its use without known efficacy.

*2.6. Previous studies by our group*

In a web-based survey of follow-up after treatment of colorectal cancer, which was sent to all registered Dutch general surgeons, a reply from 246 surgeons treating patients for colorectal carcinoma in 105 out of 118 hospitals was received (response rate 91%; [name] (a)). The generally accepted follow-up protocol consisted of CEA measurements every 3 months in the first year and six-monthly thereafter, and ultrasound examination of the liver every 6 months. Nearly all surgeons (92%) were willing to participate in a new study of follow-up protocol. In a study of literature investigating why CEA failed to prolong survival in clinical practice, several factors that can be affected were found; both in method (e.g. threshold interpretation), timing, imaging techniques following abnormal results and logistics ([name] (b)). Based on these findings a multicenter prospective phase II trial, investigating the optimal frequency and interpretation of CEA in follow-up is ongoing (OptCEA trial; METc 2207/015 UMCG, METC P07-034 MST.). Preliminary data (manuscripts in preparation) confirm that the feasibility of a follow-up study without a computer support system is difficult. This trial is one of the bases of our study, because with the results of this trial we were able to define the best flowchart to optimize the protocol and construct a large multi-center prospective study design. However, a phase III trial including the cost-effectiveness of the new follow-up scheme is not performed yet. The abdominal CT has been proven highly valuable. Routine staging with chest CT has not led to improvement in survival and neither to a better quality of life. A staging chest CT should not be done as a routine procedure in patients with either colon or rectal carcinoma. A concurrent study has been undertaken investigating the psychological effects of intensive follow-up and optimal communication towards the patient (Reijnen). A computerized follow-up system to support the more complex organisation of the study protocol has been developed and already implemented in the UMCG. Initial experiences are good. Most patients and doctors accept this new method and no practical problems have occurred at this time. Preliminary data show a large decrease in workload for the doctors and much convenience with patients because of the earlier communication of the blood results. In the Netherlands a prospective continuous data measurement (audit) of all colorectal cancer patients has started January 1st 2009 (http://www.dsca.nl). The principal investigator is part of the scientific committee and this data base can be used as a reference for the present clinical study.

**3. OBJECTIVE**

The aim of the current study is to develop an evidence-based guideline with standard diagnostic tools (CEA and CT scan) that results in a (cost-) effective recommendation which is applicable for all hospitals in the routine follow-up after curative treatment of colorectal cancer. All patients after a curative resection of the primary tumour (including a radical resection of synchronous metastases) and fit to undergo major surgery again if needed are eligible for this study.

**4. Endpoints**

*4.1. Primary endpoint*

The increased percentage of patients with intended curative metastasectomy of liver- and lung metastases from colorectal carcinoma in the intensified follow-up schedule.

*4.2. Secondary endpoints*

1) Overall survival, disease specific survival, disease free survival

2) Calculation of the optimal threshold values and measurement frequency of CEA

3) The correlation between CEA and helical CT abdomen/thorax: specifically whether the metastasis can be localized when CEA values suggest metastatic disease.

4) Evaluation of the effects of the follow-up protocol: psychological effects and logistic effectuation

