## *6.4. Sample size calculation*

Given current usual care with pre-operative staging with CT of the thorax and abdomen and neo-adjuvant therapies, the expected occurrence of metachronous metastases is approximately 25%. Of these, the expected percentage of resected metastases in patients is 10% in the control group and 25% in the intervention group. Given a significance level of 5% and a power of 80%, 115 patients with metastases in both groups are needed. Given an expected recurrence rate of 25%, 460 patients per group are needed.

Because in this study the moment to start the intervention instead of patients will be randomized, we calculated a correction factor C. Assuming a standard deviation in the effect of hospitals on the outcome of 0.1, C has a value of 1.71. (van Houwelingen) Therefore about 800 patients per group are needed.

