## 8. METHODS

## *8.1. Study parameters/endpoints*

### *8.1.1. Main study parameter/endpoint*

Percentage of patients with curative metastasectomy of liver- and lung metastasis from colorectal carcinoma in the study period: July 2010 – October 2012.

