# 10.STATISTICAL ANALYSIS

In the clinical study, the main analysis will be based on the differences between care as usual (pre-treatment) and care after implementation of the CEA watch (post-treatment) regarding the percentage of patients with resected metastases, using a multilevel model to adjust for the clustering. For the quality of life data the same analysis will be applied. In addition, potential confounders such as age, gender and tumour status will be considered.

In an economic evaluation, costs and outcomes of both follow-up strategies will be assessed and compared. Research question in the economic evaluation: “What is the incremental cost-effectiveness of a computer based (CEA-watch) follow-up protocol, compared to follow-up care as usual?” Results of the cost-effectiveness analysis will display the additional costs per additional patient with curative metastasectomy. In addition, a cost-utility analysis will be conducted, based on the quality adjusted life years (QALYs). Both types of analyses will be conducted in order to be able to estimate the balance between costs and effects on health, survival and quality of life. Costs will be studied from a societal perspective, during a time period maximally 3 years. Since the time horizon of the study exceeds one year, both costs and effects beyond the first year will be discounted, using various discounting rates of 3%, 4% and 5%, and no discounting, to facilitate international comparison of study results.

Bootstrapping will be performed on the cost and effect pairs in order to calculate confidence intervals. Cost effectiveness acceptability curves will be constructed to illustrate the probability that the different follow-up strategies will be cost-effective, given different monetary values per additional unit of health (patient with patient with curative metastasectomy/QALY).

Relevant cost components of both follow-up strategies will be assessed for all included patients. Main cost categories will be ultrasound, CT-scan, colonoscopy, CEA assay, ‘CEA watch’ system, additional diagnostic tests, outpatient visits, hospital admissions and travel expenses.

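### The primary endpoint is stated differently in four operative sections, three of which name no denominator, and the recurrence denominator used for the sample size is found by the schedule under test

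*Protocol*

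**What the plan says.** Four places in the protocol act as a definition of the primary outcome.

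- Summary, Endpoints: "increase of 15 percent of radical resected metastases in patients as expressed as the percentage of total recurrences".
- Section 4.1: "The increased percentage of patients with intended curative metastasectomy of liver- and lung metastases from colorectal carcinoma in the intensified follow-up schedule".
- Section 8.1.1: "Percentage of patients with curative metastasectomy of liver- and lung metastasis from colorectal carcinoma in the study period", which it dates July 2010 to October 2012.
- Section 10, main analysis: the comparison of the two periods is made "regarding the percentage of patients with resected metastases, using a multilevel model to adjust for the clustering".

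Section 6.4 sizes the trial. It first puts the occurrence of metachronous metastases at about 25%, then states: "Of these, the expected percentage of resected metastases in patients is 10% in the control group and 25% in the intervention group". It obtains 115 patients with metastases per group, divides by a recurrence rate of 25% to reach 460 patients, and applies a correction factor C of 1.71 for hospital-level randomisation to reach about 800. Section 2.1 puts local recurrence at about 25% of first recurrences.

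**The concern.** The four statements differ in what counts as a success, at which sites, and out of whom. A resection done with curative intent that leaves residual tumour counts under Section 4.1 but not under the Summary. A radical resection of a peritoneal deposit counts under the Summary and Section 10 but not under Sections 4.1 and 8.1.1. An analyst who follows one section can get a different result from an analyst who follows another, and the choice could be made after the data are seen. A statistical analysis plan could choose one definition, but it would have to overrule parts of the protocol to do so.

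The denominator raises a second question. Recurrences are counted after randomisation, and the intervention changes CEA frequency, the trigger for extra imaging, and CT. Those are the means by which recurrence is found. Section 6.4 nevertheless uses one 25% figure for both groups. A share of detected recurrences can then change because detection changed, not because more patients were resected.

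**Working it through.** **Step 1. The wordings side by side.**

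| Place | Resection status | Sites | Denominator |
|---|---|---|---|
| Summary | radical | not restricted | total recurrences |
| Section 4.1 | intended curative | liver, lung | not named |
| Section 8.1.1 | curative, fixed window | liver, lung | not named |
| Section 10 | resected | not restricted | not named |
| Section 6.4 (sizing) | resected | not restricted | patients with metachronous metastases |

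**Step 2. Reproduce the protocol's figure.** Inputs from Section 6.4: p1 = 0.10, p2 = 0.25, significance level 5% (taken as two-sided), power 80%. With p the mean of p1 and p2, and d their difference:

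n = [1.960 √(2p(1−p)) + 0.842 √(p1(1−p1) + p2(1−p2))]² / d²

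- p = 0.175 and d = 0.15, so n = (1.053 + 0.443)² / 0.0225 ≈ 100.
- With continuity correction, (n/4)[1 + √(1 + 4/(nd))]² = 113, close to the stated 115.
- 115 / 0.25 = 460, as stated. 460 × 1.71 = 787, close to the stated 800 or so.

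The division by 0.25 shows that 10% and 25% are shares of patients with metastases or recurrence, not of all patients.

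**Step 3. The same inputs over all patients.**

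- 0.25 × 10% = 2.5% and 0.25 × 25% = 6.25%, a difference of 3.75 points.
- The formula in Step 2 gives 466 per group, or 518 with continuity correction. The recurrence version gives 100 / 0.25 = 400, or 113 / 0.25 = 452 corrected.
- After C: 466 × 1.71 = 797 and 518 × 1.71 = 886.
- 800 / 1.71 = 468 effective patients per group give 80% power for 2.5% v 6.25% (no continuity correction).

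C is carried over unchanged. Its formula is not in the protocol, so it was not re-derived.

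**Step 4. Metastases and recurrences are not the same set.** Section 6.4 uses 25% first for metachronous metastases and then as the recurrence rate. If the 115 are total recurrences, as in the Summary, and about 25% are local (Section 2.1), then about 0.25 × 115 ≈ 29 are local recurrences. They are in the Summary's denominator, but as local recurrences they cannot enter a liver and lung numerator.

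**Step 5. Movement of the share when nothing else changes.** Hold the resected proportion at 2.5% of all patients and vary the proportion with a detected recurrence. The protocol gives only 25%; the other values are assumed.

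| Detected recurrence | Resected share of recurrences |
|---|---|
| 20% | 2.5 / 20 = 12.5% |
| 25% | 2.5 / 25 = 10% |
| 30% | 2.5 / 30 = 8.3% |

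**The case against.** The strongest reply is that this is loose wording rather than rival estimands. Sections 6.1 and 6.2 equate curative with R0 resection, and footnote 1 ties curative treatment to radical treatment confirmed by pathology. Section 10 uses curative metastasectomy for its cost-effectiveness outcome, so its bare mention of resection may be shorthand. The Summary and Section 6.4 could supply the base that the other sections omit. Part of this stands: there are at most two denominators, and curative and radical may mean the same thing. But the cited lines concern the initial treatment. Intended curative in Section 4.1 remains a different event, the site restriction appears in two of the four places only, and no passage says which base Section 10 uses.

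It can also be said that the detection effect is illustrated rather than measured, and that finding more recurrences would lower the share and so work against the intervention. Both are fair. The documents give no detected proportion by period, so neither the size nor the direction is established.

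Some stronger readings are tempting but not supported:

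- A reader might count Section 2.4, which adds the peritoneal cavity, as a further endpoint. It is background and is labelled a relevant clinical outcome, not the primary one.
- A reader might apply 10% and 25% to liver and lung recurrences only (40% + 30% in Section 2.1), scale both rates down, and conclude that power is lost. Section 6.4 applies the rates to all patients with metachronous metastases, so this is not a protocol assumption.
- A reader might infer that a mismatched denominator leaves the trial badly undersized. Step 3 shows that it does not.

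**Conclusion.** The point holds as an inconsistency in the main estimand. Four operative statements disagree on resection status and sites, three of them name no denominator, and the sample size fits only a denominator of metastases or recurrences. The same assumed effect is 15 percentage points on one base and 3.75 on the other.

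The recurrence base is also a post-randomisation count that depends on the schedule under test. The movement from 10% to 8.3% or 12.5% rests on assumed detected proportions of 30% and 20%; it shows that the share can move, not by how much it will.

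The harm is an unfixed definition that can be chosen late, not a shortage of patients: 797 to 886 per group against about 800, given the protocol's rates and an unchanged C. Nor does an all-patient proportion cure everything. A reader might take it to be independent of detection, but a metastasis is resected only once it is found, so earlier detection within a fixed window can raise that proportion too.

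**What to change.** Put one definition, in the same words, in the Summary and Sections 4.1, 6.4, 8.1.1 and 10:

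- One resection status, for example achieved R0, which agrees with radical in the Summary.
- One list of sites, applied to both numerator and denominator, with the place of local recurrence stated.
- One primary denominator, named in advance. Analyse and report both the proportion of all registered patients resected and the share of recurrences, whichever is primary. The second is reported alongside; it should not become an added condition for success unless a test, an alpha and joint power are specified.
- A sentence stating that the all-patient proportion removes the detection-dependent denominator but can still rise through earlier detection within the July 2010 to October 2012 window.

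If the all-patient version is made primary, restate Section 6.4 as 2.5% v 6.25% and re-derive C, because the hospital standard deviation of 0.1 would have to be reconsidered on that scale.

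The cost is protocol wording and one further analysis of data already collected. Achieved R0 may yield somewhat fewer successes than intended curative resection. The cost in power is small: 466 v 400 patients per group before C, or 518 v 452 with continuity correction.
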